#### 8.4.1 Laboratory evaluations

Laboratory samples will be collected at time points as indicated in [Table 5](#) Schedule of Assessments.

Local laboratory will be used for analysis of scheduled safety labs.

A midstream urine sample (approx. 30 mL) will be obtained, in order to avoid contamination with epithelial cells and sediments and allow proper assessments.

Clinically significant abnormalities must be recorded as either medical history/current medical conditions or adverse events as appropriate.

In the case where a laboratory range is not specified by the protocol, but a value is outside the reference range for the laboratory at screening and/or baseline, a decision regarding whether the

result is of clinical significance or not shall be made by the investigator (in consultation with the sponsor or designate) and shall be based, in part, upon the nature and degree of the observed abnormality. The assessment may be repeated once prior to randomization.

In all cases, the investigator must document in the source documents, the clinical considerations (i.e., result was/was not clinically significant and/or medically relevant) in allowing or disallowing the participant to continue in the study.

All abnormal lab results must be evaluated for criteria defining an adverse event and reported as such if the criteria are met. For those lab adverse events, repeated evaluations are mandatory until normalization of the result(s) or until the result is no longer considered to be clinically significant.

**Table 7: Clinical laboratory parameters collection plan**

| Test Category                               | Test Name                                                                                                                                                                                                                                                                                                                                                                                                                                                                                                       |
|---------------------------------------------|-----------------------------------------------------------------------------------------------------------------------------------------------------------------------------------------------------------------------------------------------------------------------------------------------------------------------------------------------------------------------------------------------------------------------------------------------------------------------------------------------------------------|
| Hematology                                  | Hematocrit, Hemoglobin, MCH, MCHC, MCV, Platelets, Red blood cells (RBC), White blood cells (WBC), RBC Morphology, Differential (Basophils, Eosinophils, Lymphocytes, Monocytes, Neutrophils, Bands, Other (absolute value preferred, %'s are acceptable)                                                                                                                                                                                                                                                       |
| Chemistry                                   | Albumin, Alkaline phosphatase by Fractionated Alkaline Phosphatase , ALT, AST, Gamma-glutamyl-transferase (GGT), Lactate dehydrogenase (LDH), Bicarbonate, Calcium, Magnesium, Phosphorus, Chloride, Sodium, Potassium, Cr, Creatine kinase, Direct Bilirubin, Indirect Bilirubin (only if total bilirubin is abnormal), Total Bilirubin, Total Cholesterol, LDL, HDL, Total Protein, Triglycerides, Blood Urea Nitrogen (BUN) or Urea, Uric Acid, Amylase, Lipase, Glucose (choose as applicable: non-fasting) |
| Urinalysis                                  | Macroscopic Panel (Dipstick) (Color, Bilirubin, Blood, Glucose, Ketones, Leukocytes esterase, Nitrite, pH, Protein, Specific Gravity, Urobilinogen)
If the dipstick is abnormal, then Microscopic Panel (RBCs, WBCs, Casts, Crystals, Bacteria, Epithelial cells)                                                                                                                                                                                                                                            |
| Coagulation                                 | Prothrombin time (PT), International normalized ratio [INR]), Partial thromboplastin time (PTT), Activated partial thromboplastin time (APTT)                                                                                                                                                                                                                                                                                                                                                                   |
| Thyroid                                     | T3 [free], T4 [free], TSH                                                                                                                                                                                                                                                                                                                                                                                                                                                                                       |
| Hepatitis markers                           | HBsAg, HBcAb, HCV (HCV - RNA)                                                                                                                                                                                                                                                                                                                                                                                                                                                                                   |
| Additional tests                            | SARS-CoV-2 seropositivity or SARS-COV2 PCR or Rapid Test per local site policy                                                                                                                                                                                                                                                                                                                                                                                                                                  |
| Pregnancy test and assessments of fertility | Luteinizing hormone (LH) and follicle stimulating hormone (FSH) (female only as outlined in Section 8.4.3 Pregnancy and assessments of fertility )                                                                                                                                                                                                                                                                                                                                              |

### 8.4.3 Pregnancy and assessments of fertility

Women of childbearing potential are excluded from this study.

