| KEY INCLUSION/
EXCLUSION CRITERIA
(Healthy Adults ≥18-39) | 
KEY INCLUSION
 

• Male or female aged 18 – 39 years inclusive

• Provide written informed consent to participate

• Healthy participants without acute or chronic, clinically significant pulmonary, cardiovascular, hepatic or renal functional abnormality

◦ As determined by medical history, physical exam, laboratory screening

• Body Mass Index 18-35 kg/m2, inclusive, at screening

• Females should fulfill one of the following criteria:

◦ At least one year post-menopausal,

◦ Surgically sterile,

◦ Will use oral, implantable, transdermal or injectable contraceptives during the screening window and until 60 days after vaccination

◦ Willing to use a form of highly effective contraception approved by the Investigator (e.g., intrauterine device (IUD), female condom, diaphragm with spermicide, cervical cap, use of condom by the sexual partner or a sterile sexual partner) for study duration and until 60 days after vaccination.

• Women of childbearing potential must have a negative urine pregnancy test at screening and within 24 hours preceding receipt of vaccination

• Male participants must be surgically sterile (e.g., vasectomy) or agree to practice highly effective contraception from the vaccination until 60 days after vaccination.

 
KEY EXCLUSION CRITERIA
 

• Any medical condition that in the judgement of the investigator would make subject participation in the study unsafe.

• Having cancer or received treatment for cancer within three years (persons with a history of cancer who are disease-free without treatment for three years or more are eligible), excluding basal cell carcinoma (BCC) or squamous cell carcinoma (SCC), which are allowed unless located at the vaccination site.

• Impaired immune responsiveness (of any cause), including diabetes mellitus.

 |                |   |                                                 |                |   |    |       |   |    |        |   |    |         |

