## 5.1 Inclusion Criteria

1. Male or female aged 18 – 39 years, inclusive at screening.
2. Provide written informed consent to participate in the trial.
3. Participants who, in the opinion of the investigator, can and will comply with the requirements of the protocol.
4. Healthy participants without acute or chronic, clinically significant pulmonary, cardiovascular, hepatic or renal functional abnormality
  - a. as determined by medical history, physical exam, laboratory screening
5. Body Mass Index 18-35 kg/m^2, inclusive, at screening.
6. Females should fulfill one of the following criteria:
  - At least one year post-menopausal,
  - Surgically sterile,
  - Will use oral, implantable, transdermal or injectable contraceptives during the screening window and until 60 days after vaccination
  - Willing to use a highly effective method of contraception approved by the Investigator for study duration and until 60 days after vaccination
7. Women of childbearing potential must have a negative urine pregnancy test at screening and within 24 hours preceding receipt of vaccination.
8. Male participants must be surgically sterile (e.g., vasectomy) or agree to practice highly effective method of contraception from screening until 60 days after vaccination.
9. Vital signs within following range:
  - a. oral temperature <100.0°F (37.8°C),
  - b. pulse <100 bpm,
  - c. Systolic blood pressure (SBP) ≤ 150 to 85 mmHg
10. Clinical screening laboratory evaluations (White Blood Cells [WBCs], hemoglobin [Hgb], platelets [PLTs], Alanine Transaminase [ALT], Aspartate Transaminase [AST], Creatinine [Cr], Alkaline Phosphatase [ALP], Total Bilirubin [T. Bili], Lipase, Prothrombin Time [PT], Partial Thromboplastin Time [PTT]) are within acceptable normal reference ranges at the clinical laboratory being used or determined to not be clinically significant in the opinion of the investigator.

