#### **6.2.2.1 Restrictions to prevent pregnancy**

Non-clinical reproductive toxicity studies have not yet been performed to date with VX-103. It is unknown if there is any potential impact on a pregnancy by VX-103. Therefore, sexually active males and females participating in this clinical trial are required to use highly effective contraception methods.

The following highly effective methods of contraception are accepted:

- Established use of oral, intravaginal, or transdermal combined (estrogen and progestogen containing) hormonal contraception associated with inhibition of ovulation.
- Established use of oral, injectable, or implantable progestogen-only hormonal contraception associated with inhibition of ovulation.
- Placement of an intrauterine device (IUD) or intrauterine hormone-releasing system (IUS).
- Barrier methods of contraception: male condom with either cap, diaphragm or sponge with spermicide (double barrier methods). The use of double barrier methods should always be supplemented with the use of a spermicide. Female condom and male condom should not be used together.
- Male sterilization (provided that the partner is the sole sexual partner of the patient and that the sterilized partner has received medical assessment of the surgical success.)

- Sexual abstinence

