- e. All participants will be questioned about concomitant medications at each visit. Medications taken within 30 days prior to day 1 will be documented in the eCRF. Any changes to a subject's medications will also be documented in the eCRF.
- f. The time of placement and removal of the MIMX-MAP will be recorded in the eCRF. The unblinded site staff shall refer to the pharmacy manual for specific instructions. VX-103-01 MAP should be placed on the skin for a minimum of 5 minutes and a maximum of 10 minutes
- g. Vital signs measurements include temperature, respiration rate, heart rate, and blood pressure after a 5-minute seated rest.
- h. Hematology: will be drawn and analyzed locally. The data will be captured in the eCRF and the lab reports stored with the subject's source documents at the site.
- i. Chemistry: will be drawn and analyzed locally. The data will be captured in the eCRF and the lab reports stored with the subject's source documents at the site.
- j. Female participants of childbearing potential are to have a urine pregnancy test prior to any study vaccine administration. The test result is to be recorded in the eCRF. The investigational product/products may only be administered if the pregnancy test is negative. A serum pregnancy test instead of a urine pregnancy test should only be considered if required by country, local or ethics committee regulations. If a serum pregnancy test instead of a urine pregnancy test is required by country, local or ethics committee regulations, a blood sample will be collected from women of childbearing potential at the vaccination visits and will be used for the test as per local guidance. Note: Pregnancy test must be performed even if the subject is menstruating at the time of the study visit.
- k. At minimum, a basic urine alcohol & drug screen will be used to analyze for amphetamines, Opiates, Phencyclidine (PCP), Cocaine, Marijuana, and alcohol.

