#### Assessments of fertility

Medical documentation of oophorectomy, hysterectomy, or tubal ligation must be retained as source documents. Subsequent hormone level assessment to confirm the woman is not of childbearing potential must also be available as source documentation in the following cases:

- Surgical bilateral oophorectomy without a hysterectomy
- Reported 12 months of natural (spontaneous) amenorrhea with an appropriate clinical profile.

In the absence of the above medical documentation, LH and FSH testing is required of any female participant regardless of reported reproductive/menopausal status at screening.

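### Section 8.4.3 bars women of childbearing potential, but the inclusion criteria, the synopsis and Table 5 footnote j admit them, so sites cannot follow both

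*Protocol*

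**What the plan says.** Section 8.4.3 opens with an unqualified statement: "Women of childbearing potential are excluded from this study". Its subsection on fertility assessment asks for documents showing that a woman is not of childbearing potential. Where those documents are absent, it adds that "LH and FSH testing is required of any female participant regardless of reported reproductive/menopausal status at screening". Table 7 in Section 8.4.1 carries this into the laboratory plan. Its row on pregnancy testing and fertility lists LH and FSH, points to Section 8.4.3, and names no pregnancy test.

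Section 5.1 reads differently. Criterion 6 says "Females should fulfill one of the following criteria" and gives four routes. Two are menopause and surgical sterility. The other two are contraceptive routes, one of them being "Will use oral, implantable, transdermal or injectable contraceptives during the screening window and until 60 days after vaccination". Criterion 7 adds: "Women of childbearing potential must have a negative urine pregnancy test at screening and within 24 hours preceding receipt of vaccination". The synopsis repeats criterion 7 in its key inclusion list. Table 5 footnote j in Section 8 says "Female participants of childbearing potential are to have a urine pregnancy test prior to any study vaccine administration". In Section 5.2 the only related exclusion is item 11, on pregnancy and breastfeeding.

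On contraceptive methods, the synopsis gives "use of condom by the sexual partner" as one example of a highly effective method. Section 6.2.2.1 lists barrier methods as "male condom with either cap, diaphragm or sponge with spermicide (double barrier methods".

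**The concern.** Who may be dosed is a basic term of a first-in-human protocol, and here it is stated in two incompatible ways. The population is aged 18 to 39, so the women whose eligibility is in dispute are not a marginal group. An investigator screening a woman who uses contraception and has a negative test would find her eligible under Section 5.1 and barred under Section 8.4.3. Section 6.2.2.1 says that reproductive toxicity studies have not been done with this product, so the question bears on participant protection as well as on paperwork.

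The difference over condoms concerns which methods count, not who is eligible. It would need correcting even if the main conflict did not exist.

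**Working it through.** The protocol gives no figure on this point, so no arithmetic applies. The check applies each rule in turn to every kind of female volunteer and asks whether the remaining text still makes sense.

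**Outcome by type of volunteer**

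| Volunteer | Section 5.1, criteria 6 and 7 | Section 8.4.3 |
|---|---|---|
| At least one year post-menopausal | Admitted | Admitted once confirmed |
| Surgically sterile | Admitted | Admitted once confirmed |
| Childbearing potential, accepted contraception, negative tests | Admitted | Barred |
| Childbearing potential, no accepted contraception or a positive test | Barred | Barred |

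The conflict lies entirely in the third row. For the first two rows Section 8.4.3 fits criterion 6, because it says how menopause or sterility is to be documented.

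**If Section 8.4.3 governs.** The pregnancy tests in criterion 7 and in footnote j apply to nobody. The two contraceptive routes in criterion 6 add nothing for women, since each eligible woman already qualifies by menopause or sterility.

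**If Section 5.1 governs.** The first sentence of Section 8.4.3 is false. The LH and FSH testing still stands for any woman without the listed documents, but the status it is meant to confirm is no longer needed for entry. Table 7 would also lack the pregnancy test that its own row title announces.

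**Does anything settle it?** The protocol has no clause giving one section precedence. Under Section 13.2 the investigator signs to follow all of the protocol's instructions and procedures, which cover both texts. Section 10.1.4 plans for a participant becoming pregnant, and Section 6.2.2.1 requires contraception of sexually active women. Both are consistent with enrolling women of childbearing potential, but neither withdraws Section 8.4.3.

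**What each place supplies.** Footnote j covers pregnancy testing only. The contraception conditions come from the synopsis, Section 5.1 and Section 6.2.2.1. The upper part of the Table 5 grid is not legible in the text available, so the check relies on the footnote alone.

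**Contraceptive methods.** A woman relying only on her partner's condom meets the synopsis example. She does not meet the barrier entry in Section 6.2.2.1, which requires a second barrier and spermicide.

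**The case against.** The strongest reply is that Section 5 controls eligibility. It requires all inclusion and no exclusion criteria to be met. Section 8.4.3 is not a numbered criterion, and none of the 29 exclusions mentions childbearing potential. Most of the related text is compatible with enrolling these women, so the opening of Section 8.4.3 could be a leftover sentence. The less restrictive reading also has safeguards: contraception, pregnancy testing and pregnancy follow-up.

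Much of this stands. A reader might infer that the Section 5 sentence on deviations from entry criteria makes every such enrolment a violation. It does not, because Section 8.4.3 is not among the entry criteria. The reply still does not remove the conflict. Section 8.4.3 is more than one stray sentence: it has a documentation and hormone-testing procedure that Table 7 takes up, and nothing tells a site to disregard it.

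Three other strong readings are also unsupported:

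- **Biased comparisons or different populations.** A reader might infer that sites following different rules would distort the group comparisons, or that the results would describe different populations. Randomization is central and 1:1:1, so a difference in sex mix between sites would not systematically favour a group. Nothing shows that sites would in fact diverge.
- **A count of affected participants.** This needs the female share of volunteers, which the protocol neither gives nor narrows.
- **Hormone testing of every woman.** The quoted LH and FSH clause can look universal, but it applies only where the listed documentation is absent.

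**Conclusion.** The protocol is wrong as written on this point. Section 8.4.3, with Table 7 referring to it, cannot be followed together with criteria 6 and 7, the synopsis and footnote j. This is an internal inconsistency, not a poor choice of design. The affected group is women of childbearing potential who meet the contraception and testing conditions.

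No number of participants can be attached. That the two rules differ greatly in effect rests on one assumption, that few women aged 18 to 39 are post-menopausal or surgically sterile. The contradiction itself is textual and needs no assumption. What is at stake is a clear rule on who may be exposed, not the validity of comparisons between groups. The difference over condoms is real but smaller, and adds no weight to the main point.

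**What to change.** Reconcile six places: the synopsis, Section 5.1 items 6 and 7, Section 6.2.2.1, Table 5 footnote j, Table 7 and Section 8.4.3. All should state one eligibility rule, the fertility and pregnancy testing that goes with it, and one contraception list.

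- If women of childbearing potential are eligible, the opening of Section 8.4.3 and the purpose of its hormone testing need rewording, and Table 7 should name the pregnancy test.
- If they are not eligible, criteria 6 and 7, the synopsis and footnote j need rewording, and Section 5.2 should list the exclusion.

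The clinical team decides which rule and which contraception list apply; this review takes no position. The cost is amendment wording, with the approvals described in Section 14.1 and a matching change to any site eligibility checklist. It is cheapest before enrolment starts. Sample size and analysis do not change.

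### Section 8.4.3 excludes women of childbearing potential whom the synopsis, inclusion criteria 6 and 7 and Table 5 admit, and the synopsis accepts single-barrier contraception that Section 6.2.2.1 does not

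*Protocol*

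**What the plan says.** On who may enter, Section 8.4.3 is unconditional: "Women of childbearing potential are excluded from this study". Under its subheading on fertility, it asks for documents of sterilising surgery and, in two named situations, for hormone confirmation. Where the documents are lacking, "LH and FSH testing is required of any female participant regardless of reported reproductive/menopausal status at screening". Table 7 points to this section for LH and FSH.

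Other parts of the protocol plan for the same women to take part:

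- Inclusion criterion 6 (Section 5.1, repeated in the synopsis) offers females four alternative routes. Two are post-menopausal status and surgical sterility; the other two are contraceptive use.
- Inclusion criterion 7: "Women of childbearing potential must have a negative urine pregnancy test at screening and within 24 hours preceding receipt of vaccination". The synopsis has the same rule.
- Table 5, footnote j: "Female participants of childbearing potential are to have a urine pregnancy test prior to any study vaccine administration". Product may be given if the result is negative.
- Section 5.2 has no exclusion for childbearing potential. Criterion 11 bars only pregnancy and breastfeeding.

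On methods, the synopsis gives an intrauterine device and then "female condom, diaphragm with spermicide, cervical cap, use of condom by the sexual partner or a sterile sexual partner" as examples of highly effective contraception. Section 6.2.2.1 lists "Barrier methods of contraception: male condom with either cap, diaphragm or sponge with spermicide (double barrier methods" and requires a spermicide in addition.

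**The concern.** The two sets of rules give opposite answers to a basic eligibility question, and both are written as operative text. The population is aged 18 to 39, so the literal exclusion would affect most of the women a site might screen. Section 8.4.3 also goes beyond its opening sentence: it sets a hormone-testing requirement for women whose own entry criterion does not ask them to show that they cannot conceive.

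Section 6.2.2.1 says that reproductive toxicity has not been studied and that any effect on pregnancy is unknown. Staff therefore need one entry rule and one list of accepted methods to apply at screening and explain at consent. As written, a volunteer can qualify under one section and fail under another, and a monitor can record a deviation either way.

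**Working it through.** The protocol gives no figure to reproduce on this point. The check sets the texts side by side.

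**1. Entry rule.**

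| Place | Woman of childbearing potential |
|---|---|
| Section 8.4.3, opening sentence | Excluded |
| Section 8.4.3, fertility text | LH/FSH test unless sterility or amenorrhea is documented |
| Synopsis, key inclusion | Admitted with contraception and negative pregnancy tests |
| Section 5.1, criteria 6 and 7 | Admitted on the same terms |
| Table 5, footnote j | Tested, then dosed if negative |
| Section 5.2 | Not excluded |

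One sentence excludes and three places expressly admit. Section 6.2.2.1 fits with admission, since it requires contraception of sexually active females, but it does not name these women and is not counted.

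**2. A single volunteer.** Take a woman of 25 who uses an oral contraceptive and has two negative pregnancy tests. She meets criteria 6 and 7 and no exclusion, and footnote j allows dosing. Under Section 8.4.3 she is ineligible. She also has no documents of sterility or amenorrhea, so she must have LH and FSH measured. No entry criterion refers to either hormone, so for her the test settles nothing that Section 5 asks.

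**3. Barrier methods.** The synopsis names four single barriers: female condom, diaphragm with spermicide, cervical cap and partner's condom. Section 6.2.2.1 accepts a male condom combined with a cap, diaphragm or sponge, plus spermicide, so it accepts none of the four alone (4 against 0). It mentions the female condom only to warn against using it together with a male condom. Criterion 6 in Section 5.1 gives no barrier examples, so this conflict is between the synopsis and Section 6.2.2.1.

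**4. Timing of contraception.**

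- Male start: the synopsis has men "agree to practice highly effective contraception from the vaccination until 60 days after vaccination"; criterion 8 has them "agree to practice highly effective method of contraception from screening until 60 days after vaccination". The gap is the screening window, 0 to 30 days, all before dosing. A man who meets criterion 8 also meets the synopsis.
- End: for men and for the hormonal route, the synopsis and Section 5.1 both give 60 days after vaccination. For the fourth female route, both give study duration together with the 60-day limit. The two places agree for each group.

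**The case against.** The best defence is that Section 5 governs. It requires all inclusion criteria and no exclusion criterion to be met, and Section 5.2 contains no such exclusion. Sites would therefore probably enrol these women and treat Section 8.4.3 as leftover text. That is a fair prediction of conduct, and it limits the consequences. It does not remove the contradiction: nothing in the protocol says that Section 8.4.3 yields, and its LH/FSH requirement is a separate instruction that Section 5 does not cancel. The rows of Table 5 that might show when hormones are tested are not legible in the text available, so the testing point rests on Section 8.4.3 and Table 7.

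The safety stakes are also modest. There is one dose, and pregnancy is tested at screening and within 24 hours before it.

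A reader might go further in three ways that the document does not support:

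- **That the end of contraception differs between sections**, because Section 6.2.2 opens by referring to the duration of the study. That phrase says how long participants are to be informed and reminded. Section 6.2.2.2, under the same heading, sets shorter limits of its own: 24 hours after Day 1 for alcohol and Study Day 8 for marijuana.
- **That 60 days is too short**, because Section 8.4.4 reports tip clearance in minipigs by day 90. The protocol nowhere ties contraception to tip clearance, and that passage does not address reproductive risk.
- **That the male start is a safety gap.** It lies wholly before exposure, and the stricter criterion 8 covers it.

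**Conclusion.** The contradiction over women of childbearing potential stands on the wording alone, as does the conflict over barrier methods. Section 8.4.3 is a wrong operative rule, not a missing detail, and should be corrected.

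The size is one excluding sentence against three admitting places, and four single-barrier examples against none accepted alone. How many participants are affected depends on how many women are screened and on what contraception they use, and the protocol gives neither. The conclusion assumes that the sponsor intends to enrol these women. The entry criteria, the pregnancy tests and the contraception rules all point that way.

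The male start date and the wording of the fourth female route are editorial matters. No estimate, test or sample size changes.

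**What to change.** 1. Delete the exclusion sentence in Section 8.4.3 and refer instead to the pregnancy-test rule of inclusion criterion 7.
2. In the fertility text, limit the catch-all LH/FSH requirement to women who claim post-menopausal or sterile status without the listed documents. The two situations named there for hormone confirmation can stay.
3. Remove the single-barrier examples from the synopsis, and have the synopsis and inclusion criteria 6 and 8 refer to the list in Section 6.2.2.1.
4. Editorial: start male contraception at screening in the synopsis, as in criterion 8, and state plainly in criterion 6 when contraception ends on the fourth route.

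Under Section 14.1 this needs a written amendment approved by the sponsor, the IRB/IEC and, where required, health authorities. Consent text needs to match. It adds no visit or procedure and reduces LH/FSH testing. Volunteers who rely on a single barrier would need a second method or, for the female condom, a different one.
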